#### Renal replacement therapy (RRT)

The operational definition of RRT will incorporate any form of extracorporeal renal support or replacement for patients with documented AKI. By protocol and in order to minimize the potential bias of clinician discretion on when to initiate RRT, at least one of the following criteria must be fulfilled prior to initiation of RRT: 1) refractory oliguria (urine output <100 mL in preceding 4 hrs, despite fluid resuscitation and/or vasoactive therapy F OR maximum dose of study drug); 2) refractory extravascular fluid overload AND/OR hypoxemia AND/OR pulmonary edema (FiO2 ≥60%, receiving mechanical ventilation, PaO2/FiO2 ratio ≤200); 3) azotemia (urea ≥30 mmol/L); 4) metabolic acidosis (pH <7.2 or HCO3 <15); hyperkalemia ([K^+^] ≥6.0 mmol/L or electrocardiogram changes, despite maximum dose of study drug AND/OR administration of at least 1 dose of potassium binder AND/OR intravenous insulin AND/OR intravenous bicarbonate; 5) uremia-induced organ toxicity (i.e. encephalopathy, pericarditis).

#### Renal recovery

The operational definition of renal recovery will be the return of serum creatinine to within 10% of baseline levels and a spontaneous urine output ≥1.0 mL/kg/hr for a minimum of 24 hours independent of RRT.

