**Figure 2 F2:**
[figure not shown]
**Overview of the SPARK study drug infusion algorithm**.

The study infusion bag will contain 2000 mg of furosemide in 500 mL of 0.9%NaCl for a final concentration of 4 mg/mL. The appearance of the study infusion bags for furosemide and placebo will be identical and there will be no marking on the infusion bags other than a 4-digit coded identifying study number. This will minimize bias and ensure blinding of allocation by the study investigators, research coordinator, ICU physicians and all involved health care providers.

The continuous infusion will be titrated to achieve a target urine output in the range of 1.0-2.0 mL/kg/hr. The treatment algorithm for titration of the continuous infusion is shown in Figure 2. Each patient will be administered a loading dose of 0.4 mg/kg as a separate infusion bag followed by a continuous infusion commenced at a dose of 0.05 mg/kg/hr (Table 1). The maximum infusion rate will be 0.40 mg/kg/hr. The urine output will be assessed hourly. If the target urine output has been achieved, then the current infusion rate will be continued. If the target urine output has not been achieved, the dose will be increased to the next infusion rate in the algorithm. If the urine output is too brisk (>2 mL/kg/hr x 2 hrs), the infusion rate will be reduced. If the urine output is still >2 mL/kg/hr AND the infusion rate is at the lowest rate, the study drug will be discontinued infusion until the urine output is <1 mL/kg/hr. If any of the following criteria are fulfilled: decrease in mean arterial pressure <65 AND/OR addition of or an increase in vasoactive requirements of ≥20% to achieve goal mean arterial pressure OR central venous pressure <8 cmH2O OR central venous oxygen saturation <60% OR a cardiac index <2.0 L/min/1.73 m^2 ^(if measured) at any time, the consultant ICU physician and ICU team will be notified to review the patient.

**Table 1 T1:** Summary of weight-based categories for commencement for study infusion rate (concentration study drug 4 mg/mL)

Weight Category (kg)	Bolus loading dose	Start infusion dose	Start infusion dose (mg/hr)	Start infusion rate (mL/hr)
≤50	0.4 mg/kg	0.05 mg/kg/hr	2.5	0.6

55	0.4 mg/kg	0.05 mg/kg/hr	2.8	0.7

60	0.4 mg/kg	0.05 mg/kg/hr	3.0	0.8

65	0.4 mg/kg	0.05 mg/kg/hr	3.3	0.8

70	0.4 mg/kg	0.05 mg/kg/hr	3.5	0.9

75	0.4 mg/kg	0.05 mg/kg/hr	3.8	0.9

80	0.4 mg/kg	0.05 mg/kg/hr	4.0	1.0

85	0.4 mg/kg	0.05 mg/kg/hr	4.3	1.1

90	0.4 mg/kg	0.05 mg/kg/hr	4.5	1.1

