≥95	0.4 mg/kg	0.05 mg/kg/hr	4.8	1.2

An estimate of patient ideal body weight (IBW) will be used to determine the urine output target. Determination of estimated IBW will be based on the formula described by Devine[45] (Table 2). From this estimated IBW, patients will be divided into 5 kg weight categories to determine urine output goals for protocol simplicity (Table 3). At any time during the trial, if the responsible ICU physician believes that the administration of furosemide is urgently indicated (i.e. new pulmonary edema), it can be administered and this event will be documented.

**Table 2 T2:** Devine formulate for ideal body weight estimation[45].

Sex	Devine Formula				
Female	IBW (kg) = [45 +(0.91 x (height in cm - 152))]				

Male	IBW (kg) = [50+ (0.91 x (height in cm - 152))]				

					

**Height (cm)**	**Height (feet)**	**Female**		**Male**	
		
		**IBW (kg)**	**Category**	**IBW (kg)**	**Category**

≤152	≤5'0	45	≤50	50	≤50

155	5'1	47.7	≤50	52.7	55

157	5'2	49.6	≤50	54.6	55

160	5'3	52.3	55	57.3	60

163	5'4	55.0	55	60.0	60

165	5'5	56.8	60	61.8	65

168	5'6	59.6	60	64.6	65

170	5'7	61.4	65	66.4	70

173	5'8	64.1	65	69.1	70

175	5'9	65.9	70	70.9	75

178	5'10	68.7	70	73.7	75

180	5'11	70.5	75	75.5	80

183	6'0	73.2	75	78.2	80

185	6'1	75.0	75	80.0	80

188	6'2	77.8	80	82.8	85

191	6'3	80.5	85	85.5	90

193	6'4	82.3	85	87.3	90

196	6'5	85.0	85	90.0	90

≥ 198	≥ 6'6	86.9	90	91.9	95

**Table 3 T3:** Summary of weight-based urine output targets.

Weight Category (kg)	Target Urine Output (mL)			
	
	Hourly	Per 6 hours	Per 12 hours	Per 24 hours
≤50	50-100	300-600	600-1200	≥ 1200

55	55-110	330-660	660-1320	≥ 1320

60	60-120	360-720	720-1440	≥ 1440

65	65-130	390-780	780-1560	≥ 1560

70	70-140	420-840	840-1680	≥ 1680

75	75-150	450-900	900-1800	≥ 1800

80	80-160	480-960	960-1920	≥ 1920

85	85-170	510-1020	1020-2040	≥ 2040

90	90-180	540-1080	1080-2160	≥ 2160

≥ 95	95-190	570-1140	1140-2280	≥ 2280

All other aspects of patient management within the parameters outlined (i.e. methods of fluid resuscitation, choice of fluids, vasoactive therapy, choice of vasoactive therapy, adjuvant therapies such as hrAPC, intensive insulin therapy) will be at the discretion of the consultant ICU physician. No other interventions will be performed.

The study drug infusion will be continued for a minimum of 24 hrs and discontinued if any one of the following events occurs:

• The patient is initiated on RRT;

• The patient is discharged from the ICU;

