• The patient recovers kidney function;

• The patient dies;

• The patient develops a recognized adverse reaction potentially related to the study infusion; or

• The patient has received a total of 7-days of study drug administration.

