### Data Collection

Detailed clinical, procedure-related, physiologic and laboratory data will be collected. Blood and urine will be collected at baseline, 12 hours, 24 hours and daily thereafter until participants exits the study. Data will be collected on standardized CRFs developed by the EPICORE centre. Completed CRF will be returned to the EPICORE centre, entered into a central database, where data queries will be generated.

Clinical data captured will include demographics, co-morbidities and prescribed/current drug therapy. Details of admission diagnoses, surgical status, and dates of hospital and ICU admission will be recorded. Detailed data will be recorded on date of enrollment (i.e. fulfilling criteria for early AKI). This will include details of interventions (i.e. mechanical ventilation, vasoactive drugs, fluid therapy), hemodynamics (i.e. blood pressure, heart rate, central venous pressure), and acute physiology (i.e. components of severity of illness scores, urine output, fluid balance, secondary non-kidney organ dysfunction). During the trial, data will be collected daily on urine output, fluid balance, electrolytes, acid-base status, serum creatinine and urea. Collected blood and urine samples will be stored for batched analysis of kidney-injury specific biomarkers, including: serum and urine cystatin C, serum and urine neutrophil gelatinase-associated lipocalin (NGAL), urine interleukin-18 (IL-18); urine kidney injury molecule-1 (KIM-1), and urine L-type fatty acid binding protein (L-FABP).

Data will be collected each day on whether the primary endpoint (progression of AKI) has occurred, for evidence of any secondary endpoints and for criteria for trial discontinuation.

Finally, any study protocol violations will be recorded. The adjudication of protocol violations will be determined by a study investigator blinded to the treatment allocation.

All enrolled patients will be followed to determine the duration of AKI, continued need for RRT, renal recovery and mortality until death or discharge from hospital and at 30, 60 and 90-days after randomization.

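### The urine-output part of the renal recovery definition equals the floor of the furosemide titration target and can be judged on drug, so the secondary recovery comparison can be biased towards furosemide

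*Protocol article*

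**What the plan says.** Under Operational Definitions, the Renal recovery entry has two parts joined by *and*: "the return of serum creatinine to within 10% of baseline levels and a spontaneous urine output" at or above the stated rate. The urine part in full is "a spontaneous urine output ≥1.0 mL/kg/hr for a minimum of 24 hours independent of RRT". RRT is excluded by name. Study drug and other diuretics are not mentioned, and *spontaneous* is not defined.

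Under Study Intervention: "The continuous infusion will be titrated to achieve a target urine output in the range of 1.0-2.0 mL/kg/hr". Table 3 turns this into volumes. The 70 kg row, for example, ends "420-840 840-1680 ≥ 1680" mL for 6, 12 and 24 hours. The same section lets the ICU physician give open-label furosemide when it is urgently indicated.

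The list of events that end the infusion includes "The patient recovers kidney function" and "The patient has received a total of 7-days of study drug administration".

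Objectives names the rate of renal recovery among the key secondary endpoints. Statistical Analysis compares it as a proportion by Fisher's exact test. Data Collection says that patients are "followed to determine the duration of AKI, continued need for RRT, renal recovery and mortality until death or discharge from hospital" and again at 30, 60 and 90 days.

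**The concern.** A recovery endpoint should measure kidney function. Here one of its two components is the quantity that the active drug is adjusted hourly to produce, at the same threshold. Saline under the same algorithm has no diuretic action. Two patients with the same creatinine course can therefore be classified differently only because one receives a diuretic.

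The Background of the article shows why the two should be kept apart. The systematic review it cites found a greater rise in urine output with loop diuretics (OR 2.6, p = 0.004) but no difference in renal recovery (OR 0.88, p = 0.5).

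Two situations are the most exposed:

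- **Timing of recovery during the infusion.** A furosemide patient whose creatinine has returned can meet the urine part at once, while a placebo patient waits for unaided output to reach 1.0 mL/kg/hr.
- **Patients who entered on urine output alone.** The definition of early AKI admits them without a creatinine rise. Some may have creatinine within 10% of baseline already, and for them recovery rests on urine output only.

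The trial is meant to inform a phase III design, so a spurious recovery signal would carry forward.

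**Working it through.** **The plan's own figure.** The article gives no expected recovery rate. Its only design calculation is for the primary outcome, 60% v 40% progression, and that reproduces.

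- Uncorrected n per arm = [1.96·√(2·0.5·0.5) + 0.842·√(0.6·0.4 + 0.4·0.6)]² / 0.20² = 96.9, so 97.
- With continuity correction: (96.9/4)·[1 + √(1 + 4/(96.9·0.20))]² = 106.7, so 107 per arm and 214 in total, as stated. This was raised to 216, or 108 per arm.
- Exact power of Fisher's test at 108 per arm is 80.2%.

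The present point does not touch this calculation.

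**Are the two thresholds the same?** Divide the 24-hour target in Table 3 by weight and by 24:

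- 50 kg: 1200/50/24 = 1.0 mL/kg/hr
- 70 kg: 1680/70/24 = 1.0 mL/kg/hr
- 95 kg: 2280/95/24 = 1.0 mL/kg/hr

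Every other row gives 1.0 as well. Table 3 uses ideal body weight. The recovery definition does not name its weight basis, so the match is exact if the same weight is used.

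**Can recovery be judged on drug?** Recovery is an event that ends the infusion, so it must be assessable while a patient is still under the infusion protocol. Nothing in the definition requires the 24 hours of urine output to be off drug.

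**How large could the bias be?** Let c be the proportion whose creatinine returns to within 10% of baseline, equal in both arms (no true effect). Let u be the proportion of those placebo patients who also meet the urine part. Recovery is then c·u on placebo and c·u_F on furosemide, where odds(u_F) = 2.6 × odds(u).

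The values of c and u are assumptions. The 2.6 is borrowed from the review cited in the Background, where it describes a rise in urine output rather than this threshold. All recoveries are treated as judged on drug. Rejection is the exact probability that a two-sided Fisher test gives p < 0.05 at 108 per arm.

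| c | u | u_F | Placebo | Furosemide | Difference (points) | Rejection |
|---|---|---|---|---|---|---|
| 30% | 40% | 63.4% | 12.0% | 19.0% | 7.0 | 24% |
| 30% | 60% | 79.6% | 18.0% | 23.9% | 5.9 | 14% |
| 30% | 80% | 91.2% | 24.0% | 27.4% | 3.4 | 6% |
| 30% | 95% | 98.0% | 28.5% | 29.4% | 0.9 | 4% |
| 50% | 40% | 63.4% | 20.0% | 31.7% | 11.7 | 44% |
| 50% | 60% | 79.6% | 30.0% | 39.8% | 9.8 | 28% |
| 50% | 80% | 91.2% | 40.0% | 45.6% | 5.6 | 10% |
| 50% | 95% | 98.0% | 47.5% | 49.0% | 1.5 | 4% |
| 70% | 40% | 63.4% | 28.0% | 44.4% | 16.4 | 67% |
| 70% | 60% | 79.6% | 42.0% | 55.7% | 13.7 | 46% |
| 70% | 80% | 91.2% | 56.0% | 63.9% | 7.9 | 18% |
| 70% | 95% | 98.0% | 66.5% | 68.6% | 2.1 | 5% |

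Example for c = 50%, u = 60%: odds 0.6/0.4 = 1.5; 1.5 × 2.6 = 3.9; u_F = 3.9/4.9 = 79.6%; recovery 0.5 × 0.6 = 30.0% v 0.5 × 0.796 = 39.8%.

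Two cases with the urine rates set directly and c = 50%:

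- Urine part met by 80% v 50%: recovery 40% v 25%, rejection 60%.
- Urine part met by 90% v 80%: recovery 45% v 40%, rejection 9%.

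Fisher's test is conservative. With truly equal rates of 20% to 40% it rejects in about 3.5% of trials, so the 4% to 5% results mean almost no inflation.

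**The case against.** **Creatinine must also recover.** This stands as a limit. A reader might infer that diuresis alone can produce recovery. It cannot in a patient whose creatinine is still raised; it only clears the second of two hurdles. The exception is the patient who entered on urine output with creatinine already near baseline.

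***Spontaneous* naturally means not driven by a drug.** This may be the intention, but it is not written. A reader might go further and infer that the off-drug reading makes the stopping event unreachable. That is too strong. The algorithm suspends the infusion when output stays above 2 mL/kg/hr at the lowest rate, until it falls below 1 mL/kg/hr. A patient who keeps at least 1.0 mL/kg/hr for 24 hours during that pause, with creatinine back, would satisfy both passages. This covers only a few patients, so the ambiguity remains for the rest.

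**The infusion lasts at most 7 days, and follow-up runs to 90 days.** This stands. Recovery after the infusion is judged off study drug, so timing is affected more than eventual recovery, and late follow-up dilutes the bias.

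**The size rests on assumptions.** This stands too. Patients whose creatinine has normalised probably make more urine unaided, which moves the result towards the small end of the table. Nor does the cited review (recovery OR 0.88) show a spurious benefit in practice.

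**Strictness by itself is no error.** A urine threshold stricter than leaving the Risk class applies to both arms. The problem is only that it coincides with the drug's target.

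**Conclusion.** The point holds as a risk of bias in one key secondary endpoint. The urine component of recovery has the same threshold as the titration floor, it is not restricted to time off diuretics, and it can be met on drug. The comparison of recovery can therefore lean towards furosemide with no difference in kidney function.

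Under the assumptions shown, the lean is about 1 to 16 points, with a false-positive probability of about 4% to 67%. The middle case is 30.0% v 39.8%, at 28%. It is negligible if nearly all placebo patients with recovered creatinine reach 1.0 mL/kg/hr unaided. Because all recoveries are treated as judged on drug, the figures describe on-drug assessment and overstate the effect on recovery by day 90.

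A reader might also infer that the duration of AKI is biased in the same way, or that early deaths would shorten it. The article does not support either inference. It does not define AKI duration, does not tie its end to this recovery definition, and does not say how deaths are counted. Such detail may properly sit in the full protocol or analysis plan. A bias from deaths would also need mortality to differ between the arms.

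**What to change.** For the analysed endpoint, choose one of two definitions and fix it before unblinding:

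- creatinine within 10% of baseline, sustained for 24 hours and free of RRT; or
- the present definition, with the urine component counted only over hours off both study drug and open-label diuretic.

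Under either choice, report the creatinine and urine components separately by arm.

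Report recovery separately for patients who entered on urine output alone with creatinine already near baseline. A creatinine-only definition would count them as recovered at entry, possibly while still oliguric.

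The Renal recovery definition and the recovery item in the list of infusion-ending events must be reconciled on whether recovery is judged on or off study drug. This review takes no position on what the stopping rule should be. The change proposed here concerns the analysed endpoint only.

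**Cost.** The change needs new wording and a little more analysis. Creatinine and urine output are already collected daily, and open-label furosemide is documented. The off-drug option also needs infusion start, pause and stop times. The downside is that recoveries may be counted later or be fewer in number. The primary endpoint and the sample size do not change.

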#### Systemic inflammatory response syndrome (SIRS)

The SIRS criteria include the presence of any 2 of the following: temperature >38°C or <36°C; heart rate >90 beats/min; respiratory rate >20 breaths/min or PaCO_2 _<32 mmHg or mechanically ventilated; and/or white cell count >12,000 cells/mm^3^, <4,000 cells/mm^3 ^or with >10% immature (band) forms[43].

#### Sepsis

The operational definition of the clinical syndrome of sepsis will be the presence of confirmed or suspected infection and the presence of ≥ 2 SIRS criteria.

### Inclusion Criteria

Patients must fulfill all of the following inclusion criteria:

• Peripheral or central intravenous catheter and urinary catheter

• Early AKI

• ≥ 2 criteria for the systemic inflammatory response syndrome (SIRS) within 24 hours

• Achieved immediate resuscitation goals (as directed by the treating physician) including fluid resuscitation AND/OR vasoactive therapy to achieve mean arterial pressure ≥65 mmHg, central venous pressure ≥8 cmH2O, central venous oxygen saturation ≥70% (if measured) AND/OR cardiac index ≥2.5 L/min/1.73 m^2 ^(if measured).

### Exclusion criteria

The following conditions will lead to ineligibility for study entry:

• Age <18 years

• Confirmed or suspected pregnancy (verified by serum [β-HCG] pregnancy test if necessary)

• Obstructive etiology for AKI

• ≥ Stage 4 chronic kidney disease (defined by an estimated glomerular filtration rate <30 mL/min/1.73 m^2^), end stage kidney disease on chronic RRT, kidney transplantation or already received RRT in ICU

• Resolving AKI, defined as a ≥25% or ≥44.2 μmol/L decline from peak increase in serum creatinine

• Acute pulmonary edema requiring urgent use of furosemide or RRT or patient already receiving continuous furosemide infusion

• Patient is moribund with expected death within 24 hours

• Known or suspected drug allergy to furosemide

• Enrolled in concomitant randomized trial

• Prior enrollment in SPARK

### Trial Protocol

#### Description of Study Flow

Figure 1 outlines the study flow. Patients will be identified in the ICU by daily surveillance by the research coordinator or when identified by the treating ICU physician. Each patient's eligibility will be verified by use of a one-page checklist that summarizes the inclusion and exclusion criteria. This checklist will be included in the standardized case-report form (CRF).

**Figure 1 F1:**
[figure not shown]
**Overview of patient flow**.

### Study Intervention

Patients will be commenced on a continuous infusion of either the intervention (furosemide) or identical placebo (0.9% NaCl). The study protocol for administration of furosemide by continuous infusion is adapted from the phase I study by Ostermann et al [44] (Figure 2).

**Figure 2 F2:**
[figure not shown]
**Overview of the SPARK study drug infusion algorithm**.

The study infusion bag will contain 2000 mg of furosemide in 500 mL of 0.9%NaCl for a final concentration of 4 mg/mL. The appearance of the study infusion bags for furosemide and placebo will be identical and there will be no marking on the infusion bags other than a 4-digit coded identifying study number. This will minimize bias and ensure blinding of allocation by the study investigators, research coordinator, ICU physicians and all involved health care providers.

The continuous infusion will be titrated to achieve a target urine output in the range of 1.0-2.0 mL/kg/hr. The treatment algorithm for titration of the continuous infusion is shown in Figure 2. Each patient will be administered a loading dose of 0.4 mg/kg as a separate infusion bag followed by a continuous infusion commenced at a dose of 0.05 mg/kg/hr (Table 1). The maximum infusion rate will be 0.40 mg/kg/hr. The urine output will be assessed hourly. If the target urine output has been achieved, then the current infusion rate will be continued. If the target urine output has not been achieved, the dose will be increased to the next infusion rate in the algorithm. If the urine output is too brisk (>2 mL/kg/hr x 2 hrs), the infusion rate will be reduced. If the urine output is still >2 mL/kg/hr AND the infusion rate is at the lowest rate, the study drug will be discontinued infusion until the urine output is <1 mL/kg/hr. If any of the following criteria are fulfilled: decrease in mean arterial pressure <65 AND/OR addition of or an increase in vasoactive requirements of ≥20% to achieve goal mean arterial pressure OR central venous pressure <8 cmH2O OR central venous oxygen saturation <60% OR a cardiac index <2.0 L/min/1.73 m^2 ^(if measured) at any time, the consultant ICU physician and ICU team will be notified to review the patient.

**Table 1 T1:** Summary of weight-based categories for commencement for study infusion rate (concentration study drug 4 mg/mL)

Weight Category (kg)	Bolus loading dose	Start infusion dose	Start infusion dose (mg/hr)	Start infusion rate (mL/hr)
≤50	0.4 mg/kg	0.05 mg/kg/hr	2.5	0.6

55	0.4 mg/kg	0.05 mg/kg/hr	2.8	0.7

60	0.4 mg/kg	0.05 mg/kg/hr	3.0	0.8

65	0.4 mg/kg	0.05 mg/kg/hr	3.3	0.8

70	0.4 mg/kg	0.05 mg/kg/hr	3.5	0.9

75	0.4 mg/kg	0.05 mg/kg/hr	3.8	0.9

80	0.4 mg/kg	0.05 mg/kg/hr	4.0	1.0

85	0.4 mg/kg	0.05 mg/kg/hr	4.3	1.1

90	0.4 mg/kg	0.05 mg/kg/hr	4.5	1.1

≥95	0.4 mg/kg	0.05 mg/kg/hr	4.8	1.2

An estimate of patient ideal body weight (IBW) will be used to determine the urine output target. Determination of estimated IBW will be based on the formula described by Devine[45] (Table 2). From this estimated IBW, patients will be divided into 5 kg weight categories to determine urine output goals for protocol simplicity (Table 3). At any time during the trial, if the responsible ICU physician believes that the administration of furosemide is urgently indicated (i.e. new pulmonary edema), it can be administered and this event will be documented.

**Table 2 T2:** Devine formulate for ideal body weight estimation[45].

Sex	Devine Formula				
Female	IBW (kg) = [45 +(0.91 x (height in cm - 152))]				

Male	IBW (kg) = [50+ (0.91 x (height in cm - 152))]				

					

**Height (cm)**	**Height (feet)**	**Female**		**Male**	
		
		**IBW (kg)**	**Category**	**IBW (kg)**	**Category**

≤152	≤5'0	45	≤50	50	≤50

155	5'1	47.7	≤50	52.7	55

157	5'2	49.6	≤50	54.6	55

160	5'3	52.3	55	57.3	60

163	5'4	55.0	55	60.0	60

165	5'5	56.8	60	61.8	65

168	5'6	59.6	60	64.6	65

170	5'7	61.4	65	66.4	70

173	5'8	64.1	65	69.1	70

175	5'9	65.9	70	70.9	75

178	5'10	68.7	70	73.7	75

180	5'11	70.5	75	75.5	80

183	6'0	73.2	75	78.2	80

185	6'1	75.0	75	80.0	80

188	6'2	77.8	80	82.8	85

191	6'3	80.5	85	85.5	90

193	6'4	82.3	85	87.3	90

196	6'5	85.0	85	90.0	90

≥ 198	≥ 6'6	86.9	90	91.9	95

**Table 3 T3:** Summary of weight-based urine output targets.

Weight Category (kg)	Target Urine Output (mL)			
	
	Hourly	Per 6 hours	Per 12 hours	Per 24 hours
≤50	50-100	300-600	600-1200	≥ 1200

55	55-110	330-660	660-1320	≥ 1320

60	60-120	360-720	720-1440	≥ 1440

65	65-130	390-780	780-1560	≥ 1560

70	70-140	420-840	840-1680	≥ 1680

75	75-150	450-900	900-1800	≥ 1800

80	80-160	480-960	960-1920	≥ 1920

85	85-170	510-1020	1020-2040	≥ 2040

90	90-180	540-1080	1080-2160	≥ 2160

≥ 95	95-190	570-1140	1140-2280	≥ 2280

All other aspects of patient management within the parameters outlined (i.e. methods of fluid resuscitation, choice of fluids, vasoactive therapy, choice of vasoactive therapy, adjuvant therapies such as hrAPC, intensive insulin therapy) will be at the discretion of the consultant ICU physician. No other interventions will be performed.

The study drug infusion will be continued for a minimum of 24 hrs and discontinued if any one of the following events occurs:

• The patient is initiated on RRT;

• The patient is discharged from the ICU;

• The patient recovers kidney function;

• The patient dies;

• The patient develops a recognized adverse reaction potentially related to the study infusion; or

• The patient has received a total of 7-days of study drug administration.

